### Trial design {8}

This is an exploratory, monocentric, controlled, randomized, crossover, clinical study to detect potential biomarkers. Each participant will be allocated in randomized order to each of the three study arms (control, sleep restriction, and sleep deprivation). Due to the nature of the study, blinding is not possible among participants and study personnel. Test assessors will be blinded, however.

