Secondary outcome measures will include:i.Driving performance: Investigators will gather driving simulation results via Standardized Application for Fitness to Drive Evaluations (S.A.F.E.) [17–19], and analyze their changes after sleep deficit in comparison to the control condition. Driving simulation test is scheduled once per study arm, in the morning after the experimental night (10 am).ii.Psychomotor vigilance test (PVT) [20]: The PVT is a gold standard reaction time test to assess vigilance and sustained attention. It will be performed after arrival at the study site (6 pm, baseline), repeatedly during scheduled wakefulness (8 am, 12 pm, 4 pm, 7 pm, 11 pm), and in the morning after recovery night (8 am).iii.d2 Test of Attention [21, 22]: The d2 Test of Attention is a paper and pencil test to assess selective and sustained attention and visual scanning speed. It is scheduled after arrival at the study site (6 pm, baseline), repeatedly during scheduled wakefulness (8 am, 12 pm, 4 pm, 7 pm, 11 pm), and in the morning after recovery night (8 am).iv.Visual attention test [23]: The visual attention test is a virtual reality glasses test to assess visual skills in a complex visual environment. It will be conducted after arrival at the study site (8 pm, baseline), repeatedly during scheduled wakefulness (10 am, 2 pm, 6 pm, 8 pm), and in the morning after recovery night (8 am).v.Subjective situational sleepiness: Participants will complete the Karolinska Sleepiness Scale (KSS) [24] questionnaire after arrival at the study site (6 pm, baseline), repeatedly during scheduled wakefulness (8 am, 12 pm, 4 pm, 7 pm, 11 pm), and in the morning after recovery night (8 am).vi.Subjective sleepiness: Participants will complete the Stanford Sleepiness Scale (SSS) [25] questionnaire after arrival at the study site (6 pm, baseline), repeatedly during scheduled wakefulness (8 am, 12 pm, 4 pm, 7 pm, 11 pm), and in the morning after recovery night (8 am).vii.Electroencephalographic (EEG) changes: Investigators will analyze changes in sleep and wake EEG patterns of participants by calculating sleep scores according to the American Academy of Sleep Medicine (AASM) scoring manual [26]. EEG recordings will be performed during scheduled sleep, driving simulation test (10 am), and at two time points during scheduled wakefulness (12 pm, 7 pm).viii.Behavioral markers of drowsy driving: Investigators will examine participants immediately after the driving simulation test for behavioral abnormalities concerning orientation, coordination, speech, mood, appearance, reaction, and pupillary light reflex.ix.Changes in metabolite concentrations in exhaled breath: Investigators will collect exhaled breath samples from participants for quantification of all detectable metabolites after arrival at the study site (8 pm, baseline), repeatedly during scheduled wakefulness (10 am, 2 pm, 6 pm, 8 pm, 11 pm), and in the morning after recovery night (8 am). They will analyze which metabolite concentration values undergo significant changes during sleep deficit conditions sessions in comparison to the control condition and also show the effects of recovery sleep. These will serve as secondary candidate biomarkers.x.Changes in metabolite concentrations in finger sweat: Investigators will collect finger sweat samples from participants for quantification of all detectable metabolites after arrival at the study site (8 pm, baseline), repeatedly during scheduled wakefulness (10 am, 2 pm, 6 pm, 8 pm, 11 pm), and in the morning after recovery night (8 am). They will analyze which metabolite concentration values undergo significant changes during sleep deficit conditions sessions in comparison to the control condition and also show the effects of recovery sleep. These will serve as secondary candidate biomarkers.xi.Correlation of metabolic changes between blood and non-invasive specimens: Investigators will compare metabolite concentrations in non-invasive matrices (oral fluid, finger sweat, exhaled breath, and dried blood spots) and compare those with a blood sample. The collection of specimens for this outcome is scheduled immediately after the driving simulation test in each study arm.

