## Statistical methods

### Statistical methods for primary and secondary outcomes {20a}

Based on our study design, statistical analysis will be performed to detect both intra- and inter-individual (i.e., individual and group) differences. All the analyses will be carried out in reference to hours of wakefulness (i.e., clock time), and also in reference to the internal body time (IBT) of the participants which is determined by the dim light melatonin onset (DLMO) from oral fluid samples.

The primary outcome of the trial is the changes detected in the metabolome. Concentration values of metabolic features will be used to generate feature time series. As a first characterization, the rhythmicity of features will be tested by cosinor analysis. Other regression models such as linear, exponential, or logarithmic functions will be applied for fitting time series data in order to simplify complex patterns. To extract relevant features from the time series, different statistical approaches will be carried out. Firstly, we will investigate how group-level differences vary when applying generalized linear mixed models and — if group-level differences exist — conduct multiple comparison tests. After applying the corrections for multiple testing (Benjamini–Hochberg procedure, i.e., false discovery rate), adjusted p-values will be considered significant when below 0.05. Significant features will then be shortlisted. Secondly, each time series will be checked for the occurrence of regular patterns (e.g., linear increase/decrease, exponential, etc.) in relation to hours of wakefulness. Again, each feature candidate will be added to the shortlist. Lastly, a classification task will be carried out to isolate those features leading to a separation between the study arms. The result of the primary outcome will be a list of candidate biomarkers.

For secondary outcomes, differences between study groups will be reported. For variables that are continuous (i.e., outcome of PVT, d2-task, driving simulator parameters, EEG data) the mean and the median will be computed accordingly. For variables that are either binary or ordinal (i.e., results of the behavioral impairment test, visual attention test, sleepiness scales, expert decision on driving ability), the relative frequencies, proportions, and standard errors for each group will be reported.

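### The summaries fixed for the secondary performance and sleepiness outcomes give no precision for the within-participant change from control

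*Protocol article*

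**What the plan says.** Trial design {8} sets out a crossover: "Each participant will be allocated in randomized order to each of the three study arms". The three study groups are therefore the same men.

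Outcomes {12} states the aim for driving performance as a contrast; investigators will "analyze their changes after sleep deficit in comparison to the control condition".

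Statistical methods {20a} opens with a general promise: "statistical analysis will be performed to detect both intra- and inter-individual (i.e., individual and group) differences". For the metabolome it names a model that can carry within-participant dependence: "we will investigate how group-level differences vary when applying generalized linear mixed models". For the rest it says: "For secondary outcomes, differences between study groups will be reported". It then names the statistics:

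- Continuous variables (PVT, d2, driving simulator parameters, EEG): "the mean and the median will be computed accordingly".
- Binary or ordinal variables (behavioural impairment test, visual attention test, sleepiness scales, expert decision on driving ability): "the relative frequencies, proportions, and standard errors for each group will be reported".

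The comparison of blood with the other matrices has its own regression in the same section and is not part of this point.

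**The concern.** The section promises differences and intra-individual analysis, but the statistics it names for the performance and sleepiness outcomes describe levels. For the binary and ordinal outcomes the only measure of uncertainty named belongs to a single arm. For the continuous outcomes none is named.

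The trial wants a biomarker panel that indicates sleepiness and its behavioural consequences, so how far each man's performance moves from his own control level is a central result. Driving is tested only once per arm, so no repeat measurements can make up for an imprecise contrast. A report that followed the text literally would show three arm summaries and leave the reader unable to judge how well either change from control is estimated. The reader's natural shortcut, combining two arm standard errors, gives up the gain in precision for which each man acts as his own control.

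**Working it through.** **Inputs**

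- Participants: 24 planned (Sample size {14}).
- Arms: three, all taken by the same men (Trial design {8}).
- Within-man correlation between conditions, ρ: not given. Assumed range 0.3 to 0.7, with 0 for reference.
- Effect sizes and event rates for secondary outcomes: not given. Those below are illustrations.

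**The plan's own figure.** No precision or power figure is stated for any secondary outcome, so there is none to reproduce. The stated minimum of 17 participants concerns metabolite quantities. It draws on pilot data compared by a paired t-test, and the effect size behind it is not given.

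**Step 1: what arm standard errors can and cannot give.** For arms 1 and 2 measured in the same men:

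- Correct SE of the difference = √(SE₁² + SE₂² − 2ρ·SE₁·SE₂)
- SE if the arms are combined as independent = √(SE₁² + SE₂²)

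The arm summaries supply SE₁ and SE₂ but not ρ, so the first line cannot be computed from them. With equal variances the second exceeds the first by the factor 1/√(1−ρ).

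**Step 2: size for a measure with standard deviation 1, n = 24.** The independent version is √(2/24) = 0.289 whatever the correlation. The paired version is √(2(1−ρ)/24).

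| Assumed ρ | Paired SE | Independent SE | Ratio |
|---|---|---|---|
| 0 | 0.289 | 0.289 | 1.00 |
| 0.3 | 0.242 | 0.289 | 1.20 |
| 0.5 | 0.204 | 0.289 | 1.41 |
| 0.7 | 0.158 | 0.289 | 1.83 |

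**Step 3: a binary example.** This is the class for which arm standard errors are actually fixed. Assume a sign in 25% of men under control and 50% under sleep deficit, n = 24.

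- Arm SEs: √(0.25 × 0.75/24) = 0.088 and √(0.50 × 0.50/24) = 0.102.
- Combined as independent: √(0.088² + 0.102²) = 0.135.
- Paired, with correlation φ between the two binary results: √[(0.1875 + 0.25 − 2φ√(0.1875 × 0.25))/24] = 0.113 for φ = 0.3 and 0.096 for φ = 0.5.
- Ratios: 0.135/0.113 = 1.19 and 0.135/0.096 = 1.41, close to Step 2.

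**Step 4: power, as an illustration for continuous measures only.** Take a true difference of 0.5 standard deviations, n = 24, two-sided 5%.

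- A paired t-test has 65% power at ρ = 0.5 and 86% at ρ = 0.7.
- By simulation, an unpaired test applied to the same correlated data has about 36% and 33%.

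The protocol names no test for these outcomes. The figures show what pairing is worth, not what the plan will do.

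**The case against.** The strongest reply is that this is a condensed article. A paired interval or a mixed model for the secondary outcomes may stand in an analysis plan that is not shown, and the absence of such detail would not be a fault. The text also gives signs that the design is understood: {20a} opens with intra-individual differences, it says that differences will be reported, and the pilot comparison was paired. The mean and median are not expressly said to be per arm, so they could be read as summaries of differences. A standard error per arm is a valid descriptive statistic, and the trial is labelled exploratory.

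Much of this stands, and it rules out several stronger readings that a reader might draw:

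- **That the arms are analysed as if they were different people.** No unpaired test is named, and the opening sentence of {20a} points the other way.
- **That all secondary outcomes carry misleading error bars.** Group standard errors are fixed only for the binary and ordinal outcomes.
- **That repeated occasions are pooled as if independent, giving standard errors that are too small.** Pooling is nowhere stated, and {20a} refers its analyses to hours of wakefulness.
- **That a sign seen in no one would be reported with a standard error of zero.** This presumes both a particular formula and a particular result, and the document gives neither.
- **That the link between biomarkers and performance is invalidated.** That link is assigned to cross-correlation analyses, which do not use the arm standard errors.

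The reply does not remove the core. The section does choose methods: mixed models with false discovery rate control for the metabolome, and regression for the matrix comparison. For the performance and sleepiness outcomes it chooses summaries whose only stated uncertainty is per group. That is a mismatch within the text shown, between the contrast promised and the statistics named to deliver it.

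**Conclusion.** The point holds in a limited form. For the binary and ordinal secondary outcomes the text fixes a standard error for each group, and for the continuous ones a mean and a median with no measure of error. None of these gives the precision of the within-participant change from control, and none delivers the intra-individual analysis promised at the head of the section.

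If arm standard errors were combined as independent, the standard error of the difference would be about 1.2 to 1.8 times too large. This rests on an assumed within-man correlation of 0.3 to 0.7, equal variances and one value per man per arm. With positive correlation the error is conservative. The primary metabolome analysis is not affected. This is a free improvement to the analysis text, not a flaw in the design.

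**What to change.** State in {20a} that each secondary performance and sleepiness outcome is reported as the within-participant difference, sleep deprivation minus control and sleep restriction minus control, each with a 95% confidence interval.

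- **Continuous outcomes (PVT, d2, driving simulator, EEG):** a mixed model with participant as random effect and arm, period and, where measured repeatedly, time point as terms.
- **Binary outcomes:** a paired risk difference with its interval, or a model clustered on participant where there are several occasions.
- **Ordinal outcomes, including the sleepiness scales:** an ordinal mixed model with participant as random effect.
- **Arm means, medians, proportions and standard errors:** keep them, labelled as description only.

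If an analysis plan already specifies this, one sentence in {20a} pointing to it is enough. The cost is analysis wording and routine code. No new data, visits or participants are needed.

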### Outcomes {12}

The primary outcome of this trial is changes in the metabolic profile (i.e., metabolome) in oral fluid. Investigators will collect samples from participants for quantification of all detectable metabolites after arrival at the study site (6 pm, baseline), repeatedly during scheduled wakefulness (8 am, 12 pm, 4 pm, 7 pm, 11 pm), and in the morning after recovery night (8 am). They will analyze which metabolite concentration values undergo significant changes during sleep deficit conditions in comparison to the control condition and also show the effects of recovery sleep. These will serve as candidate biomarkers.

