Regarding the metabolic correlation between blood and non-invasive specimens as a secondary outcome, a regression analysis will be performed between metabolite concentration values in blood and in other sampled matrices.

As a last step, causality between all outcomes will be tested by cross-correlation analyses.

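### Cross-correlation cannot test causality between outcomes that share imposed drivers, and it has no lagged form for outcomes measured once per arm

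*Protocol article*

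**What the plan says.** The last analysis described in the Protocol article, section {20a}, is that "causality between all outcomes will be tested by cross-correlation analyses". No other causal method is named.

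The outcomes section {12} sets very different sampling densities.

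- **Oral fluid (primary), PVT, d2, KSS and SSS:** a 6 pm baseline, then "repeatedly during scheduled wakefulness (8 am, 12 pm, 4 pm, 7 pm, 11 pm), and in the morning after recovery night (8 am"). That is seven listed times per arm.
- **Wake EEG:** "EEG recordings will be performed during scheduled sleep, driving simulation test (10 am), and at two time points during scheduled wakefulness (12 pm, 7 pm").
- **Driving:** "Driving simulation test is scheduled once per study arm, in the morning after the experimental night (10 am").
- **Behavioural markers:** "Investigators will examine participants immediately after the driving simulation test for behavioral abnormalities", so once per arm.
- **Comparison of blood with the non-invasive matrices:** "The collection of specimens for this outcome is scheduled immediately after the driving simulation test in each study arm". Oral fluid is one of these matrices.

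The objectives section {7} presents the link between metabolic profiling and sleepiness-related performance impairment, driving above all, as new. For the performance outcomes themselves, section {20a} plans only summaries by study group.

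**The concern.** The sentence fixes both a conclusion (causality) and a method (cross-correlation), and the method cannot deliver the conclusion. A fuller analysis plan could add detail but could not make the statement true.

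The design supports a causal effect of sleep condition on each outcome. It gives no such support for an effect of one outcome on another, because no metabolite, reaction time or driving score is manipulated. All of them respond to the same imposed schedule. Section {20a} itself expects rhythms and trends in the metabolic features, since it plans cosinor and trend fits. Two series that share a rhythm or trend correlate whether or not one acts on the other.

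The phrase *all outcomes* also takes in outcomes that have no time series within an arm. At stake is the link between metabolites and performance: a shared sleep-loss or time-of-day signal could be read as one outcome causing another, and the route to the driving link is left unspecified.

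**Working it through.** The sentence carries no figure to reproduce. Three checks apply.

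**1. Pairs available at each lag.** Within one participant and arm, pairs at lag k = number of time points − k, using the times in section {12}.

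| Outcome | Times | Lag 0 | Lag 1 | Lag 2 | Lag 3 |
|---|---|---|---|---|---|
| Oral fluid, PVT, d2, KSS, SSS | 7 | 7 | 6 | 5 | 4 |
| Visual attention test | 6 | 6 | 5 | 4 | 3 |
| Wake EEG at 12 pm and 7 pm | 2 | 2 | 1 | 0 | 0 |
| Driving, behavioural rating, blood | 1 | 1 | 0 | 0 | 0 |

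A correlation from one pair is undefined. On a running clock the oral-fluid times are 18, 32, 36, 40, 43, 47 and 56 h, with gaps of 14, 4, 4, 3, 4 and 9 h. A lag of one sample therefore means anything from 3 to 14 hours. For a single series tested alone, the two-sided 5% critical |r| = t/√(t² + n − 2), with t on n − 2 degrees of freedom. This is 0.88 for n = 5 and 0.75 for n = 7.

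**2. Correlation produced by a shared driver alone.** The signal strengths are assumptions, since the document gives none.

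*Shared rhythm.* Two series, each cos(2π(time − phase)/24) plus independent noise, were sampled at 8, 12, 16, 19 and 23 h, with no link between them. The ranges cover all phases tried.

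| Noise SD (amplitude 1) | Mean within-participant r |
|---|---|
| 0.5 | 0.64 to 0.78 |
| 1 | 0.28 to 0.43 |
| 2 | 0.08 to 0.15 |

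If the second series peaks 6 hours later (noise SD 0.5), the mean r lies between about −0.22 and 0.22, depending on phase.

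*Shared trend.* There were 24 participants and the seven oral-fluid times, with both series following elapsed time and no link between them. The test was a one-sample t-test on the Fisher-z values, two-sided 0.05.

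| Trend (in noise SD) | Mean r, lag 0 | Significant, lag 0 | Significant, lag 1 |
|---|---|---|---|
| 0.5 | 0.22 | 74% | 28% |
| 1 | 0.55 | 100% | 99% |
| 2 | 0.84 | 100% | 100% |

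A significant lag-1 value is what a reader would take as temporal precedence. Here it arises with no link at all.

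**3. What remains possible for driving.** Across participants there are 24 pairs per arm, or 24 × 3 = 72 pooled. Within-participant arm differences (SD − C and SR − C) can be paired with the same differences in the oral-fluid sample taken right after the drive. The two differences share the control value. Under no association, pooling the 2 × 24 = 48 differences as if independent rejects in about 8 to 9% of simulated trials at a nominal 5%. Each contrast alone rejects in about 5%.

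**The case against.** The case on the other side has real weight.

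- **Exploratory, and a last step.** Section {8} calls the trial exploratory. The shortlist of candidate biomarkers comes from mixed models with Benjamini–Hochberg adjustment, pattern checks and classification, none of which uses this sentence. The discussion also says the panel still needs verification. This stands and limits the severity. It does not make a claimed causal test correct.
- **Driving can still be analysed.** A reader might infer that the driving link cannot be assessed at all. The document does not support that. It does not restrict the analysis to lagged, within-arm series, an ordinary correlation across participants is computable, and vehicle signals could be cross-correlated with the EEG recorded during the same drive. What does not exist is a lagged within-arm cross-correlation of driving with metabolites.
- **Time of day is partly handled.** Section {20a} refers all analyses to hours awake and to internal body time, and the clock times are the same in every arm, so arm contrasts at a fixed time cancel a common diurnal signal. This is fair. But choosing a time axis is not adjustment, the sentence does not describe arm contrasts, and the shared sleep-loss signal remains in them.
- **The size is assumed.** A reader might take the upper end, r near 0.8, as the expected artefact. It needs low noise and matching phase. With more noise or a 6-hour shift it is small, so only the range can be given.

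**Conclusion.** The statement is wrong as written: cross-correlation in this design can show association and at most temporal order, not causality between outcomes. That conclusion needs no assumed figure. It follows from what is randomised and from the drivers that all outcomes share.

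The size of the spurious correlation does rest on assumptions: a mean within-participant r of about 0.1 to 0.8 for a shared in-phase 24-hour cosine of amplitude 1, with noise SD from 2 down to 0.5. For driving, the behavioural rating and blood, no lagged within-arm cross-correlation with metabolites exists.

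Severity is moderate. A reader might infer that the main result is compromised, but the primary shortlist does not depend on this step. The sentence matters because it is the only stated method connecting metabolites to performance, which section {7} makes an objective.

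**What to change.** Replace *causality* with *association* in section {20a}, label the analysis exploratory, and state how each type of outcome enters.

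- **Repeatedly measured outcomes:** a mixed model of performance on the participant's metabolite deviation from his own mean and on that mean, with a random participant effect and fixed effects for clock time and period. Show it with and without arm, because adjusting for arm removes the mean sleep-loss signal that the biomarkers are meant to track.
- **Driving:** relate within-participant arm differences in the driving score to the same differences in the oral-fluid sample taken right after the drive. Analyse SD − C and SR − C separately, or in one model that accounts for the shared control value. Apply Benjamini–Hochberg adjustment across features. These differences still carry the common sleep-loss effect, so they too are reported as association.

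The cost is one sentence replaced, slightly more analysis work and a weaker stated conclusion. The data and visits stay as planned.
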